It is hypothesized that there will be a higher rate of negative appendicectomies in rural hospitals as opposed to metropolitan hospitals, rooting from various potential factors. According to an audit examining the rural–urban differences in surgical interventions in the United States (US), there were higher rates of an array of surgeries including appendicectomies in areas classified rural according to US standards. This was contrary to the authors’ hypothesis that rurally located patients would have lower surgical rates. The authors proposed this could be explained by rural patients experiencing overall poorer health, increasing the indications for many surgeries to be undertaken [8]. This can be extrapolated to the Australian setting, where, according to the Australian Institute of Health and Welfare (AIHW), risk factors such as smoking, obesity, and hypertension amongst many others all increased with rurality, as well as chronic health conditions and burden of disease [9]. Another factor which may contribute to potential higher negative appendicectomies is that doctors may have a lower threshold to perform the surgery in order to avoid potential severe complications, such as perforation in a setting where there is reduced healthcare access. This may in turn lead to reduced surgical wait times in rural settings, addressing both our primary and secondary outcomes. Another US study on pediatric patients revealed that rural hospitals were 50% more likely to perform negative appendicectomies. The authors explained this is due to negative appendicectomies being justified in order to “decrease delay in diagnosis and subsequently lower the risk of appendiceal perforation” [10]. The authors noted that this disparity may also be in part due to reduced access to pre-operative imaging such as computed tomography to make the diagnosis. It is suspected a combination of all stated factors may play a role in reduced surgical wait times and negative appendicectomies in rural compared to metropolitan hospitals in Western Australia.

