## Aim

The aim of this study was to determine the variation in appendicectomy surgery wait times between rural and urban areas in Western Australia after initial presentation and diagnosis at an emergency department. Within these populations, selected outcome measures will be examined by time from:Initial presentation for the presenting complaint at an emergency department to the patient being seen by a general surgery registrar or consultant.Time from patient being seen by a general surgery registrar or consultant to surgery being performed.

The reason for taking data based on the two separate time frames is that by recording time between initial emergency department presentation to the patient being seen by the general surgery registrar or consultant, it will be possible to account for those patients who are not immediately diagnosed and then go on to have a delayed diagnostic laparoscopy and appendicectomy and evaluate and measure the magnitude of outcome impacts that an increased duration of this time could produce. Furthermore, the case report forms collect data on previous presentations of the same presenting complaint within the past week to capture any *prior premature discharge from the same site on initial evaluation of presenting complaint*.

This will allow examination of the effect of both triage wait times and timing of surgery after diagnosis on perforation, operation duration, and length of stay amongst each of the subpopulations.

Additionally, it is hoped to establish the rate of negative appendicectomies in urban and rural areas in Western Australia and if necessary make suggestions preoperatively to reduce their incidence.

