## Methods

This protocol adheres to the reporting recommendations relevant specifically to an observational retrospective cohort study of the Guidelines for Reporting Outcomes in Trial Protocols: The SPIRIT-Outcomes (2022), obtained via the Equator Guidelines [12]. Consultation with doctors in the field of general surgery and rural health experts from WACHS was performed in the development of this protocol to ensure that the needs of rural populations are not misrepresented.

The study design was chosen to be retrospective due to the difficulties of prospective recruitment by medical student data collectors for whom it is unrealistic to conduct a prospective study to recruit appendicitis patients due to the transient nature of placements, especially in large metro hospitals, which would likely lead to selection bias (for more details, see “Collaborative teams”). Four separate 2-week data collection periods were preferred over one asynchronous period of data collection to provide structure for the data collection into four 6-month retrospective review periods which would allow more medical students to participate in data collection in the project overall if each student is allocated one data collection period and to divide the amount of retrospective data to be reviewed into a manageable amount for each mini-team (for more details see “Collaborative teams”).

The retrospective time period which will be examined for eligible patients and from which data is collected will be over a 2-year period from January 2022 to November 2023. Appendicectomy patients will be identified from the operating room register by members of the mini-teams discussed in the “Methods” section, expected to be mainly medical student data collectors currently on placement at the relevant hospital, and then, each respective hospital’s emergency room data collection subsequently will be accessed to fill out the case report forms. The data will be collated via case report forms based on demographics and clinical findings, pre-operative investigations, and management and follow-up. Case report forms with > 95% completeness will be accepted for pooled analysis. The expected duration of retrospective data collection will be 8 months. This includes the four 2-week data collection periods.

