### Data analysis

Normally distributed data will be reported as mean (standard deviation (SD)), and non-normally distributed data will be reported as median (interquartile range (IQR)). Independent *t*-tests or ANOVAs will be used for normally distributed variables, Mann–Whitney *U* and Kruskal–Wallis tests will be used for non-normally distributed continuous or ordinal variables, and chi-squared tests will be used for categorical variable comparisons. When comparing appendicectomy wait times with complication incidence during the data analysis phase, a *P* value of 0.05 will be used to determine statistical significance. There will be no interim analysis or audit planned due to the grouping of data sets over four data collection periods. As this is a retrospective observational cohort study, there are no plans to deviate from the original protocol statistical plan or study design.

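### The protocol asks for the effect of waiting and of rural versus urban care on outcomes, but names only tests without covariates

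*Protocol article*

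**What the plan says.** The Abstract and Introduction put two things into the primary aim: the rural–urban difference in wait times, and the effect of that difference on outcomes. The Aim section says the two recorded intervals will allow "examination of the effect of both triage wait times and timing of surgery after diagnosis on perforation, operation duration, and length of stay". It also says the study will measure how large the impact of a longer first interval is.

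Data analysis then assigns a test to each type of variable. For the normal case, independent t-"tests or ANOVAs will be used for normally distributed variables". For the next, Mann–Whitney and Kruskal–Wallis "tests will be used for non-normally distributed continuous or ordinal variables". Finally, "chi-squared tests will be used for categorical variable comparisons". The section gives one significance threshold: a *P* "value of 0.05 will be used to determine statistical significance". It ties this threshold to one occasion only, described as "When comparing appendicectomy wait times with complication incidence during the data analysis phase". No regression, stratification, matching or covariate is named in the article, and the section closes by saying that no departure from the statistical plan or design is intended.

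On data, Methods says: "The data will be collated via case report forms based on demographics and clinical findings, pre-operative investigations, and management and follow-up". On case mix, the Introduction reports for Australia that "risk factors such as smoking, obesity, and hypertension amongst many others all increased with rurality". It also suggests that rural doctors may operate at a lower threshold and have less access to pre-operative imaging.

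**The concern.** The aim is about effects and the named tests compare crude groups. Patients in this cohort wait different lengths of time for reasons that may also bear on their outcome, and severity at arrival is the obvious candidate. If severity shortens the wait and also raises the risk of perforation, complications and a long stay, a crude comparison mixes the two influences. Delay can then look harmless or even beneficial.

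The rural–urban comparison of outcomes has a parallel problem, and here the Introduction itself supplies the reasons to expect different patients in the two settings. At stake are two possible false conclusions: that longer waits are safe, or that a difference due to case mix is due to rural care.

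**Working it through.** **1. The plan's own figure.** Sample size states over 1600 participants. Doubling the annual claims gives 2 × 818 = 1636. The site totals give 4 × 350 + 5 × 50 = 1650. The two agree, and 1650 is used below. This is a feasibility count; the article gives no event rate or effect size.

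**2. Question against method.** The Aim section wants the size of the impact of a longer wait. A t-test, Mann–Whitney or chi-squared test, or their versions for several groups, gives a crude contrast. Used as described, none holds severity or any other characteristic fixed.

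**3. How far a crude contrast can move.** Every input here is assumed; none comes from the documents. A share *s* = 0.30 is severe at arrival. Early surgery is given to a fraction *a* of severe and *b* of other patients. Complication risk after early surgery is 0.20 if severe and 0.05 otherwise. Within each severity group the late-versus-early odds ratio is ψ.

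- Early risk = [s·a·0.20 + (1−s)·b·0.05] / [s·a + (1−s)·b]
- Late risk = [s(1−a)·r₁ + (1−s)(1−b)·r₂] / [s(1−a) + (1−s)(1−b)]
- For ψ = 1.0: r₁ = 0.20, r₂ = 0.05
- For ψ = 1.5: r₁ = 0.375/1.375 = 0.273, r₂ = 0.0789/1.0789 = 0.073

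Worked case, *a* = 0.60, *b* = 0.45, ψ = 1.0:

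- Early = (0.18 × 0.20 + 0.315 × 0.05)/0.495 = 0.0518/0.495 = 10.5%
- Late = (0.12 × 0.20 + 0.385 × 0.05)/0.505 = 0.0433/0.505 = 8.6%
- Crude odds ratio = (0.0856/0.9144)/(0.1045/0.8955) = 0.80

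| Early surgery, severe / other | True OR | Early risk | Late risk | Crude OR | Chance that the crude test is significant, N = 1650 |
|---|---|---|---|---|---|
| 50% / 50% | 1.0 | 9.5% | 9.5% | 1.00 | – |
| 50% / 50% | 1.5 | 9.5% | 13.3% | 1.46 | 68% |
| 60% / 45% | 1.0 | 10.5% | 8.6% | 0.80 | 26% |
| 60% / 45% | 1.5 | 10.5% | 12.1% | 1.17 | 18% |
| 70% / 40% | 1.0 | 11.4% | 7.6% | 0.64 | 74% |
| 70% / 40% | 1.5 | 11.4% | 10.8% | 0.94 | 6% |
| 80% / 40% | 1.0 | 11.9% | 6.9% | 0.55 | 94% |
| 80% / 40% | 1.5 | 11.9% | 9.8% | 0.80 | 28% |

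In the second row, 1.46 instead of 1.5 is not confounding: an odds ratio pooled over risk groups lies slightly nearer 1 than the one within them.

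Widening the assumptions to 20–30% severe and a severe-case risk of 15–30% gives these crude odds ratios:

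- True 1.0: 0.75–0.86 under 60%/45%, and 0.45–0.67 under 80%/40%.
- True 1.5: 1.07–1.28 under 60%/45%, 0.80–1.11 under 70%/40%, and 0.64–1.00 under 80%/40%.

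A larger sample does not reduce this bias; it makes a biased result more likely to be significant.

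**4. Length of stay.** Hospital stay length is counted from presentation at the emergency department, so it contains the wait. Even if waiting changes nothing afterwards, stay rises with the wait. This pushes the other way from step 3, and covariates do not remove it.

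**5. Rural versus urban.** The Introduction names poorer rural health, a lower threshold to operate and less imaging. Any of these could shift outcomes or the negative appendicectomy rate. The article gives no figures from which to size this.

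**The case against.** The strongest reply has four parts.

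- **Prioritisation is not in the documents.** Nothing says that sicker patients are operated on sooner. Without it the bias in step 3 is absent, and other case-mix differences could push either way. This stands, so that part of the point is conditional.
- **The article is condensed.** It does not say that the named tests are the only ones, and the sentence on complications sets a threshold without assigning a test. Covariate lists and functional form are commonly left to an analysis plan, and their absence is no fault here. But the section gives a test family for every variable type and says the plan is not expected to change. For an effect question, that is a method stated and badly fixed.
- **The defined primary outcome is descriptive.** Primary outcome measure compares wait times between rural and metropolitan hospitals. A crude comparison is a legitimate way to describe how long patients wait in each setting. This stands: the point does not reach that comparison.
- **The case report form is not shown.** Only its headings and the item on earlier presentations are known. A reader might infer that every covariate needed is already collected; the article does not establish that.

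Nor is the problem confined to two-group tests. ANOVA and Kruskal–Wallis are also named; as described, they are equally unadjusted.

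**Conclusion.** The point holds in limited form. The outcome-effect part of the aim is tied to tests without covariates, and these cannot answer it in a non-randomised cohort.

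If severe cases are prioritised, on the assumed 30% severe and risks of 20% versus 5%, a true odds ratio of 1.0 would appear as about 0.80 to 0.55, and a true 1.5 as about 1.17 to 0.80. A reader might infer that the crude analysis will reverse the sign. The documents do not support that: under weak prioritisation a true 1.5 is shrunk but keeps its direction, and reversal needs stronger prioritisation.

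The rural–urban part needs no such assumption. The Introduction itself expects patients and operating thresholds to differ, so crude differences in outcomes and in negative appendicectomy cannot be attributed to setting.

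**What to change.** In Data analysis, make multivariable regression the main analysis of wait time on each outcome, and of rural versus urban on outcomes:

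- Use logistic models for binary outcomes and log-linear models for durations.
- Allow for clustering by hospital. Setting varies only between the nine hospitals, so the rural–urban model needs a method suited to few clusters.
- Adjust for age, sex, prior presentation, and those clinical and laboratory severity items at presentation that the case report form records. Do not adjust for operative or histological grade, which is itself an outcome (Rate of complex appendicitis).
- Keep the crude tests for the descriptive rural–urban comparison of wait times, and elsewhere as secondary results.
- Keep stay as defined under Hospital stay length, but state that it contains the wait when relating it to wait time.
- Word conclusions as associations.

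The cost is modest extra modelling and somewhat wider intervals. Residual confounding remains wherever items are not recorded. Regression will also not remove a difference in operating threshold, since that changes who enters a cohort made up of operated patients; the report should say so.

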Following data collection, only case report forms with > 95% data completeness will be accepted for pooled analysis. Centers with > 5% missing data points will be excluded and collaborators from those centers withdrawn from the published list of citable collaborators. This is in order to provide some leeway for potential missing data, while also acknowledging that case report forms with ≥ 5% missing data may not be useful for our purposes. As the data originates from emergency department records, there is no perceived risk of including false or unused data. This study RGS6483 has received HREC approval by the Royal Perth Hospital HREC Ethics Committee, with a waiver of consent obtained and the HREC was notified of amendments to the protocol made on April 21, 2024.

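### Wait time is compared with complications by unstratified tests on patients from nine hospitals, so hospital differences in both usual wait and event rate would be mixed into the apparent effect of waiting

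*Protocol article*

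**What the plan says.** The Aim section of the protocol article sets out to examine how waiting affects perforation, operation duration and length of stay in each of the subpopulations, which in context are the rural and the urban patients. The Data analysis section then lists tests by type of variable. For continuous or ordinal data it gives t-tests or ANOVA if normally distributed; otherwise "Mann–Whitney *U* and Kruskal–Wallis tests will be used for non-normally distributed continuous or ordinal variables". For the rest, "chi-squared tests will be used for categorical variable comparisons". The only comparison given a threshold is the one introduced by "When comparing appendicectomy wait times with complication incidence during the data analysis phase", for which "a *P* value of 0.05 will be used to determine statistical significance". No stratum, covariate or model is named, and the section closes by saying that no departure from the plan is intended.

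The Methods section says that "only case report forms with > 95% data completeness will be accepted for pooled analysis". The Sample size section gives 350 participants at each of four metropolitan hospitals and 50 at each of five rural ones. Nothing in the article stratifies by hospital.

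**The concern.** Whether a longer wait harms a patient is best asked among patients of the same hospital. A test that sets all patients with a complication against all patients without one also compares hospitals. If the slower hospitals have more complications for reasons unrelated to waiting, patients with complications will show longer waits although waiting did nothing. If the slower hospitals have fewer complications, a real harm of waiting can be hidden, or waiting can look protective.

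This needs no confounding between patients of one hospital, so it is distinct from sicker patients being operated on sooner. What is at stake is the one comparison for which the article states a significance level, and the effect-of-waiting half of its primary aim.

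**Working it through.** **Planned numbers.** 4 × 350 = 1400 metropolitan and 5 × 50 = 250 rural, together 1650. The claims-based count is 2 × 818 = 1636. Both agree with the stated total of over 1600. Metropolitan share: 1400 / 1650 = 85%.

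**Inputs.** Hospital sizes and the 0.05 level are from the article; two-sided testing is assumed. Hospital median waits, event rates and the spread of waits within a hospital are assumptions, because the article gives none.

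**Mechanism by hand.** Suppose the four metropolitan hospitals have median waits of 14, 16, 20 and 24 h and event rates of 6, 8, 12 and 15%, with no effect of waiting in any of them.
- Expected events: 350 × (0.06, 0.08, 0.12, 0.15) = 21, 28, 42 and 52.5, total 143.5. Non-events: 1400 − 143.5 = 1256.5.
- Mean log median wait, weighted by events: 425.72 / 143.5 = 2.967, or 19.4 h. Weighted by non-events: 3629.18 / 1256.5 = 2.888, or 18.0 h.
- With a within-hospital SD of log wait of 0.6 and a between-hospital variance of 0.043, the total SD is √(0.36 + 0.043) = 0.635. The standard error of the difference is 0.635 × √(1/143.5 + 1/1256.5) = 0.056.
- The spurious shift is (2.967 − 2.888) / 0.056 ≈ 1.4 standard errors, so a nominal 5% test would reject in roughly P(Z > 1.96 − 1.4) ≈ 29% of studies.

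**Simulation with set hospital values** (4000 studies per row, log-normal waits, SD of log wait 0.6). All three tests are rank tests of wait by event: T = Σ w_k [R_k − n_1k(N_k + 1)/2], w_k = 1/(N_k + 1), divided by its standard error. Here k is the whole sample, the rural or urban group, or the hospital (van Elteren). Rejection rates with no within-hospital effect:

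| Hospital differences | Pooled | Rural-urban strata | Hospital strata |
|---|---|---|---|
| None | 0.056 | 0.057 | 0.056 |
| Waits only (18 v 14 h; 10% everywhere) | 0.052 | 0.053 | 0.052 |
| Rural-urban, mild (18 v 14 h; 10 v 15%) | 0.063 | 0.048 | 0.047 |
| Rural-urban, larger (18 v 12 h; 10 v 20%) | 0.194 | 0.049 | 0.048 |
| Metropolitan, mild (15–21 h; 8–12%) | 0.069 | 0.070 | 0.053 |
| Metropolitan, moderate (14–24 h; 6–15%) | 0.262 | 0.254 | 0.050 |
| Same spread, reversed | 0.233 | 0.236 | 0.054 |

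In the moderate row every pooled rejection says that longer waits are worse. In the reversed row almost all say that they are protective.

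**Simulation with random hospital differences** (3000 studies per setting, within-hospital SD of log wait 0.7, event rates 8% and 20%). SDs are for log median wait and log-odds of the event.

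| SDs | Pooled, no true effect |
|---|---|
| 0.2 / 0.2 | about 5 to 7% |
| 0.3 / 0.4 | 10 to 16% |
| 0.4 / 0.6 | 20 to 30% |

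The hospital-stratified test stays at about 4 to 6%. To read the SDs: over nine hospitals the expected slowest-to-fastest ratio of median wait is about 1.8, 2.4 and 3.3 for SDs 0.2, 0.3 and 0.4. The expected highest-to-lowest ratio of event odds is about 1.8, 3.3 and 5.9 for SDs 0.2, 0.4 and 0.6.

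**Power.** For a true odds ratio of 1.37 per doubling of wait (2^0.45), an 8% event rate and SDs 0.3/0.4:
- Correlation −0.7 between hospital wait and baseline risk: 0.74 pooled v 0.93 stratified if risk follows the actual wait; 0.62 v 0.93 if it follows wait relative to the hospital's usual wait.
- Correlation 0: 0.93 v 0.93.
- SDs 0.2/0.2 with correlation −0.7: 0.89 v 0.93.

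In the set-value simulation (odds ratio 1.25 per SD of log wait), power was 0.76 for all three tests without hospital differences. With the reversed spread it was 0.23 pooled v 0.75 stratified.

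**The case against.** The strongest reply concerns what the article supports. Its Introduction expects differences by rurality only: "risk factors such as smoking, obesity, and hypertension amongst many others all increased with rurality", and, on waits, "This may in turn lead to reduced surgical wait times in rural settings". It offers the health differences to explain higher surgery rates and more negative appendicectomies, not higher complication rates. The Aim already points to looking within rural and urban groups, which removes that part (0.194 to 0.049 above). No statement says that the metropolitan hospitals differ in wait or risk. This stands. A reader might infer that the article itself predicts hospital differences in both wait and complications, and that the test therefore fails its 5% level. The documents do not support that: the inflation is conditional, absent when only waits differ and slight when differences are mild.

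A reader might also infer that power is generally lost. The −0.7 correlation behind the largest loss in the random-hospital simulation has no source, and at zero correlation nothing is lost when risk follows the actual wait.

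It can also be said that the tests are listed generically, that "will be accepted for pooled analysis" is a rule for accepting forms rather than a model, and that a separate analysis plan may stratify. This carries some weight. But the article names its tests, all of them unadjusted, and states that it does not intend to deviate, so this is more than a detail left open.

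**Conclusion.** The concern holds as a conditional one. The listed analysis mixes between-hospital differences into the apparent effect of waiting whenever hospitals differ in both usual wait and event rate, and a rural-urban split leaves the differences among the metropolitan hospitals, 85% of the planned sample, untouched. The error rate may be close to nominal or several times nominal. The choice between these rests on assumed spreads, which the documents do not supply. The direction of any change in power depends equally on an unknown: whether slower hospitals have lower or higher baseline risk.

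The case for changing the plan does not require the worse settings to be true. Stratifying by hospital costs essentially no power when hospitals are alike (0.76 v 0.76) and protects the result when they are not. It is an improvement that should be made, not evidence that the planned result will be wrong.

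**What to change.** State in the Data analysis section that the effect of waiting on each outcome is estimated within hospital, by regression with hospital as a fixed effect: logistic for complications and complex appendicitis, linear on the log scale for operation duration and stay. Report the effect per doubling of wait with a 95% interval. A hospital-stratified van Elteren test may support the binary outcomes only; it compares two groups, so it cannot relate a continuous wait to duration or stay and gives no effect per doubling. Report the unstratified result alongside as secondary.

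Do not carry hospital fixed effects into the separate rural-urban comparison of waits. Each hospital is either rural or urban, so the fixed effects would absorb that contrast.

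The cost is a sentence or two. Data are collected and accepted by centre, so hospital is known for every record. The small downside is that hospitals with no events add nothing to the binary-outcome estimate. The change does not deal with patient-level confounding within a hospital, such as sicker patients being operated on sooner; that needs case-mix terms in the same model.
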